## Abstract

**Introduction:**

Public health environmental surveillance has evolved, especially during the coronavirus pandemic, with wastewater-based surveillance being a prominent example. As surveillance methods expand, it is important to have a robust evaluation of surveillance systems. This consensus study will develop an evaluation framework for public health environmental surveillance, informed by the expanding practice of wastewater-based surveillance during the pandemic.

**Methods:**

The public health environmental surveillance evaluation framework will be developed in five steps. In Step 1, a multinational and multidisciplinary executive group will be formed to guide the framework development process. In Step 2, candidate items will be generated by conducting relevant scoping reviews and consultation with the study executive group. In Step 3, an international electronic Delphi will be conducted over two rounds to develop consensus on items for the framework. In Step 4, the executive group will reconvene to finalize the evaluation framework, discuss standout items, and determine the dissemination strategies. Lastly, Step 5 will focus on disseminating the evaluation framework to all parties involved with or affected by wastewater-based surveillance using traditional and public-oriented methods.

**Discussion:**

The Delphi consensus study will provide multidisciplinary and multinational consensus for the evaluation framework, by providing a set of minimum criteria required for the evaluation of public health environmental surveillance systems. The evaluation framework is intended to support the sustainability of environmental surveillance and improve its implementation, reliability, credibility, and value.

## Introduction

Public health relies on effective surveillance systems to support informed decision-making and timely interventions [1]. Wastewater-based surveillance, a form of environmental-based surveillance, has historically informed public health responses to threats like typhoid, polio, and illicit drug use [2–6]. More recently, the coronavirus pandemic (Covid-19) marked a turning point, expanding wastewater-based monitoring and surveillance to an unprecedented scale and underscoring its potential for wider public health applications [7]. Since then, wastewater-based surveillance, has supported public health practice for controlling monkeypox [8], influenza [9,10], antimicrobial resistance [11,12], and other pathogens and health risks beyond infectious diseases [13,14]. It is now used globally across diverse settings [15], from metropolitan to rural areas [16,17]. Cited advantages include its ability to track disease transmission independently of clinical testing availability or health-seeking behaviour, offering a non-invasive, resource-efficient surveillance method [18,19].

Current frameworks for evaluating surveillance performance require reassessment and updating. Established guidelines, such as the U.S. Centers for Disease Control and Prevention (CDC) 2001 framework, were developed before widespread environmental-based surveillance and do not adequately address unique challenges like environmental measurement variability or the need for broad, multidisciplinary collaboration [5,20,21]. Meanwhile, the pandemic prompted shifts in surveillance practices—such as increased public engagement and open-access data—and encouraged consensus-driven guidance through international, multidisciplinary collaboration. Yet no systematic review has examined how these developments influence surveillance evaluation, and there is no rigorous consensus on measuring the performance of wastewater-based surveillance and other forms of environmental-based surveillance.

This study aims to develop a comprehensive public health evaluation framework. Wastewater-based surveillance will be an example; however, it will apply to broader public health environmental surveillance systems, including air and surface monitoring. Surveillance targets considered include infectious agents and health risks beyond SARS-CoV-2.

### Study objectives

This project will use a multidisciplinary and multinational consensus approach to develop an evaluation framework for public health environmental surveillance (**P**ublic **H**ealth **E**nvironmental **S**urveillance **E**valuation **F**ramework, PHES-EF). See https://PHES-EF.org. An evaluation framework provides structured guidance to facilitate a systematic approach to program evaluation [22–24]. See below for the study’s definition of an evaluation framework.

Specific objectives for the framework development process are as follows: (1) engage a multidisciplinary executive group of international experts to inform the development of the evaluation framework; (2) review the literature to identify current guidance on surveillance evaluation items; (3) prioritize items for an evaluation framework for public health environmental surveillance using an international electronic-Delphi (e-Delphi) process; (4) conduct a consensus meeting, which engages experts across disciplines, to create an evaluation framework for public health environmental surveillance based on feedback from the international e-Delphi process; and, (5) develop a comprehensive dissemination plan for the evaluation framework.

### Definitions

We define key terms as follows:

**Environmental-based surveillance (environmental surveillance):** Surveillance of substances or organisms in air, water, soil, and living organisms to detect changes or threats that may affect human health, ecosystems, or both [25].**Evaluation framework:** A structured system or schema to assess a program systematically [1,22,24]. An evaluation framework presents a clear list of items or elements that should appear in an evaluation, such as constructs or concepts. It provides an organisation or structure for the list of items, defines how the list and organisation were developed, and potentially includes details about measuring the evaluation items. Importantly, an evaluation framework facilitates informed decision-making by providing a comprehensive understanding of program effectiveness and areas for improvement.**Public health surveillance:** The ongoing systematic collection, analysis, interpretation and dissemination of health data for the planning, implementation and evaluation of public health interventions and strategies to protect and improve the health of populations [26].**Wastewater:** Water that has been in contact with people (e.g., for washing) or used for cleansing and sanitation (e.g., for flushing away faecal matter), and is discharged via sewers or other sanitation systems [6].**Wastewater-based surveillance (wastewater surveillance**): A public health approach that examines specific substances or organisms in wastewater (sewage). Wastewater surveillance can be referred to as wastewater-based epidemiology; however, the latter can be specific to using wastewater to study and analyse the distribution, patterns, and determinants of health and disease conditions in defined populations [26].

## Materials and methods

### Study design

This protocol was developed *a priori*. The development of PHES-EF is guided by recommendations for Delphi techniques in the health sciences [27]. Fig 1 provides an overview of the study flow.

**Fig 1 pone.0310342.g001:**
[figure not shown]
Overview of the development process for PHES-EF.

### Step 1: Establish the executive group

A multinational and multidisciplinary executive group will oversee the development of the evaluation framework. The group will bring expertise from various fields, including public health, infectious disease, epidemiology, environmental and physical sciences, mathematical sciences, social sciences, communication, knowledge translation and exchange, knowledge users, and an engaged public.

The composition of the study executive group, which includes content expert and knowledge user members, will be identified by examining relevant author lists, internet-based searching, and the study working group’s professional networks. In contrast, the engaged public member of the executive group will be identified through an open call for expressions of interest. The S1 Table details the composition of the study executive group.

The executive group will be responsible for providing feedback on the framework development process (e.g., framework organization, completeness, additions, redundancy), supporting and advising working groups in their area of expertise, connecting the study to other related projects, recruiting e-Delphi panellists, participating in the consensus meeting, disseminating the evaluation framework, advising and/or participating in post-publication activities, and promoting the adoption of the evaluation framework among their professional networks. Co-chairs will also be responsible for decision-making when the executive group cannot reach a consensus, leading executive group activities, and the overall framework development process.

### Step 2: Generate candidate evaluation items

We will systematically compile a list of e-Delphi candidate items through scoping reviews, content analysis and extraction, and executive group consultation.

### Scoping reviews

Two scoping reviews will be performed to provide a comprehensive view of public health environmental surveillance system evaluations. The first review will identify frameworks (e.g., sources which guide the planning, management, or conduct of processes) and criteria (e.g., principles on which a judgment may be based) for evaluating public health or environmental surveillance systems. The second review will explore insights from the Covid-19 pandemic, particularly focusing on the principles of equity, trust, open science, community engagement, and One Health in the context of wastewater surveillance [28–30]. Detailed protocols for the scoping reviews are available on OSF (https://doi.org/10.17605/OSF.IO/GSKF6; https://doi.org/10.17605/OSF.IO/C9A3Q). The completed scoping reviews will be reported following the Preferred Reporting Items for Systematic Reviews and Meta-Analyses extension for scoping reviews (PRISMA-ScR) [31]. See S1 and S2 Appendices for associated PRISMA-ScR checklists.

### Content analysis and extraction

We will conduct a content analysis on items identified during the data extraction phase for both scoping reviews. The content analyses will identify and group criteria for evaluating public health and environmental surveillance systems. In the first step, one team member will group all the extracted items into initial domains and themes. In the second step, two researchers will independently compare the category system of the first researcher to agree on the final category system consensually. In the third step, all criteria will be reviewed again to merge or modify duplicate concepts and create a parsimonious framework for the initial list of e-Delphi candidate items.

### Executive group consultation

The executive group will review the initial list of e-Delphi candidate items and discuss the initial structure and presentation of Round 1 items. Their review will focus on creating an evidence-informed public health environmental surveillance framework centred around SARS-CoV-2 wastewater surveillance, and incorporating lessons learned from the pandemic (e.g., equity, open science, community engagement, and One Health). Additional items will be added if the executive group determines that key evaluation areas have not been addressed.

### Step 3: International e-Delphi survey

A Delphi technique will be used to develop an internationally accepted evaluation framework for public health environmental surveillance. The Delphi method is an iterative multi-round approach that uses a series of sequential surveys, interspersed by controlled feedback, to elicit consensus among a group of individuals while maintaining anonymity [32,33]. An e-Delphi method will be used to overcome geographic barriers and allow us to engage panellists internationally across various time zones. Delphi surveys relating to health sciences have typically been conducted for 2–3 rounds [27,34,35]. Therefore, a two-round e-Delphi survey and a subsequent consensus meeting will be conducted to balance feasibility with rigour. Each round will be active for approximately 4–6 weeks to allow panellists sufficient time to participate in the survey while balancing study timeline constraints [36].

### Recruitment of panellists

We will recruit a multinational, multidisciplinary panel of wastewater surveillance experts, knowledge users, and engaged members of the public to complete the e-Delphi survey. Content experts are adult individuals with knowledge in their respective subdiscipline groups (see S2 Table). Panellists will be selected to capture the multiple perspectives of those that influence the design, implementation, evaluation, use, and reporting of wastewater surveillance activities, including the following subdisciplines groups: public health, infectious disease, epidemiology; environmental and physical sciences; mathematical sciences; social sciences; and communication, knowledge translation and exchange. Targeted recruitment will also be conducted to identify knowledge users and engaged members of the public. We will use purposive sampling to identify potentially eligible panellists by examining relevant author lists from the scoping reviews, professional networks, and internet-based searching, among other potential methods. Potential panellists may also be recruited using social media, a study website or calls for expressions of interest during relevant meetings, presentations, or correspondence. Snowball sampling may also be employed by executive group members and potential panellists to maximize recruitment.

Potentially eligible panellists will receive a recruitment email from the study working group, executive group members, or other potential panellists. A call for panellists to share the e-Delphi with other potentially eligible panellists may be included in recruitment materials and the e-Delphi survey. Inclusion criteria for e-Delphi panellists are outlined in Table 1.

**Table 1 pone.0310342.t001:** Eligibility criteria for e-Delphi survey panellists.

Discipline group	Discipline subgroup	Inclusion criteria
Content experts	Public health, infectious disease, epidemiology Environmental and physical sciences Mathematical sciences Social sciences Communication, knowledge translation and exchange	An adult^a^ who is proficient in English and has a graduate degree in one of the listed specializations^b^, or ≥ 3 years of professional experience, or ≥ 2 peer-reviewed publications relating to wastewater surveillance.
Knowledge users		An adult^a^ who is proficient in English and who is a professional who does not have specialized training or qualifications in wastewater surveillance, but who uses surveillance data to inform policy and action in their workplace.
Engaged public		An adult^a^ who is proficient in English and has relevant lived experience.

Definitions: (1) Professional experience – Paid employment or professional practice in a listed specialization (current or former); (2) Graduate or professional degree – Master’s or Doctor of Philosophy (PhD) relating to a listed discipline subgroup.

a Adult: ≥ 18 years of age

b See S2 Table for specializations associated with each discipline.

We will conduct an all-rounds e-Delphi invitation approach, meaning panellists will be invited to every round regardless of whether they participated in the previous round [37]. Previous Delphi studies have commonly ranged from 20 to 30 panellists; however, there is no agreed upon standard [35,38]. Studies have also shown that the number of panellists and their diversity can impact the quality of outcomes [38]. Therefore, assuming only half of registered panellists will participate in at least one round, we will aim to recruit at least 50 panellists. Preferably, with at least 8–10 people per discipline subgroup. The study working group will monitor the distribution of registered panellists based on their demographic information and will try to distribute appropriately across discipline subgroups and other demographic markers.

Registration to complete the e-Delphi will open approximately four weeks before the first round, and e-Delphi round surveys will be active for roughly 4–6 weeks. The tentative start and end dates for recruitment are 08/09/2025 and 19/12/2025, respectively. Recruitment or retention efforts will occur throughout each e-Delphi round and the four weeks of targeted recruitment before Round 1. Email reminders to complete the survey will be sent twice per e-Delphi round. Panellists may also receive up to two reminders to complete the screening questionnaire during the targeted recruitment period. The time required to complete each e-Delphi round survey will be approximately one hour. The estimated time commitment will be provided to all potential panellists during recruitment and before starting the consensus process.

### Panellist withdrawal or termination

Panellists will not be able to withdraw from the study due to the safeguards in place to maintain anonymity; however, they may choose to stop actively participating in the study at any time.

### Panellist compensation

Content experts and knowledge users who complete all rounds of the e-Delphi process will receive a $100 CAD pre-paid Visa card in compensation for the time required to complete the e-Delphi process. Engaged members of the public who complete all rounds will be entered to win one of five $100 CAD pre-paid Visa cards. Remuneration has been shown to encourage participation and retention from diverse groups, thereby minimizing bias, and motivating thoughtful, high-quality responses, thereby improving data quality [39].

### Procedure

We will conduct a two-round e-Delphi survey to generate consensus on evaluation criteria (see Fig 2). The full survey will be pre-tested and validated before administration. A pilot test of the survey will be conducted with up to five test panellists. Test panellists may include members of the executive group or other potential panellists matching our recruitment criteria. The pilot test will focus on assessing the clarity and relevance of background information provided for candidate items. The survey will be revised as necessary following feedback from pilot testing. Summaries of Round 1 will be compiled for the subsequent round.

**Fig 2 pone.0310342.g002:**
[figure not shown]
E-Delphi and consensus meeting methodology, methods to achieve consensus on core items for PHES-EF. Consensus: if ≥ 70% of panellist votes fall within the same category (irrelevant, equivocal, relevant); no consensus if <70% agreement. Item relevancy: *core item*: highly or moderately relevant; *further discussion*: slightly relevant, neutral, slightly irrelevant; *excluded item*: moderately or highly irrelevant.

We will use the Surveylet Delphi platform to administer the survey [40]. The platform facilitates interactive dialogue between panellists by allowing them to justify their responses and comment on the responses of others. Panellists can also save their progress and answer survey questions across multiple sessions. Custom survey pathways will be generated for each panellist discipline subgroup (i.e., panellists from different discipline subgroups will be shown a different collection of candidate items). Within each custom discipline subgroup survey pathway, panellists can skip items or self-declare that they are not qualified to assess certain candidate items. To ensure the independent evaluation of items, the order of candidate items may be randomized for each panellist.

Individuals will complete the screening questionnaire separate from the e-Delphi platform using LimeSurvey [41]. The study working group will review eligibility, and if eligible to participate in the study, individuals will receive an individualized link for anonymous participation in the e-Delphi survey. Implied consent will be obtained electronically for all panellists using the Surveylet Delphi platform before participation in the survey. Panellists who are eligible for compensation or wish to receive acknowledgement for their contributions will be able to do so by clicking a link at the end of each survey round. The link will bring them to a separate LimeSurvey form that will not be linked to their survey responses, allowing for e-Delphi responses to remain anonymous.

### Defining consensus

Candidate items will be assessed on the following four rating properties: (1) relevance and practical utility; (2) scientific rigor, validity and reliability; (3) feasibility, adaptability and resource implications; and (4) equity, inclusiveness, and mitigation of bias.

A 7-point Likert scale (1 = highly irrelevant to 7 = highly relevant) will be used to rate each property for all candidate items. A summary score for each candidate item will be created by calculating the median of the four property ratings. Panellist summary scores will then be categorized as excluded item (irrelevant: 1–2), further discussion (equivocal: 3–5), or core item (relevant: 6–7). Consensus for each item is defined as ≥ 70% of the panellist votes falling within the same category (1–2, 3–5, or 6–7).

The approach to use a 7-point fully-labeled Likert scale – a higher number of categories compared to many studies – is informed by the consideration that panellists are professionals and engaged members of the public with good cognitive skills; therefore, more categories and labels will be more discriminating and reproducible [42–45]. The ≥ 70% consensus cut-off – a lower cut-off compared to many studies – is informed by the rapidly evolving nature of environmental surveillance for public health and the wide range of disciplines invited to the panel; therefore, a high level of agreement may not occur [42–45].

The rating properties were synthesized from previous performance evaluation frameworks from public health and health systems [1,24,46–51]. Equity is a property that was not previously identified but was added following an expert group discussion of potential properties and the study’s goals and objectives. See S3 Appendix for further details on the rating properties for e-Delphi candidate item scoring.

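### A panellist's median of four ratings can be 2.5 or 5.5, values that none of the three consensus categories covers, so the 70% rule cannot classify some votes as written

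*Protocol article*

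**What the plan says.** All of the rule is in the protocol article, under Defining consensus, and the Fig 2 caption repeats it.

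- Ratings: "Candidate items will be assessed on the following four rating properties", and "A 7-point Likert scale (1 = highly irrelevant to 7 = highly relevant) will be used to rate each property for all candidate items".
- Score: "A summary score for each candidate item will be created by calculating the median of the four property ratings".
- Categories: "Panellist summary scores will then be categorized as excluded item (irrelevant: 1–2), further discussion (equivocal: 3–5), or core item (relevant: 6–7".
- Threshold: "Consensus for each item is defined as ≥ 70% of the panellist votes falling within the same category (1–2, 3–5, or 6–7".

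The Fig 2 caption counts whether "panellist votes fall within the same category (irrelevant, equivocal, relevant", attaches each category to whole-point labels (core means highly or moderately relevant), and adds "no consensus if <70% agreement".

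Three other sections set what follows from the result. Stopping rules ends re-rating of an item once it reaches consensus, and sends equivocal-consensus and remaining non-consensual items to the consensus meeting. Round 2 re-rates items that did not reach consensus. Step 4 has the executive group vote on the equivocal and non-consensual items.

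Nothing in the text shown gives a rounding rule, a lower- or upper-median convention, or a category for scores between 2 and 3 or between 5 and 6.

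**The concern.** The categories are written for whole numbers, but the score being categorised is not always a whole number. With an even number of ratings, the usual median is the mean of the middle two. A panellist who rates an item 5, 5, 6, 6 has a summary score of 5.5, which is neither 3–5 nor 6–7. The same happens at 2.5, on the boundary with the excluded category.

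At stake is the study's main decision rule. A vote at 5.5 could be counted as core, counted as not core, or dropped from the denominator, and the same ratings can then fall on either side of 70%. On that depends whether the survey settles an item as core or excluded, or whether the item is re-rated in Round 2 and, if still unresolved, voted on at the meeting. If the convention is not fixed beforehand, it could be chosen once the ratings are known.

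**Working it through.** The article gives no figure to reproduce on this point.

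**Inputs from the article.** Four ratings per panellist and item; integers 1 to 7; categories 1–2, 3–5, 6–7; threshold 70%. For the panel size, the recruitment section aims for at least 50 registered and assumes half take part, so 50 × 0.5 = 25 raters. The distribution of ratings is not given and is assumed below.

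**Step 1: which scores have no category.** Possible medians are 1, 1.5, 2, …, 7. The values 1.5, 3.5, 4.5 and 6.5 lie inside a stated range. Only 2.5 and 5.5 do not.

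**Step 2: how many rating sets give them.** There are 7⁴ = 2,401 ordered sets. A median of 5.5 needs the middle two ratings to sum to 11.

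- Middle pair 5 and 6: 6 × (5² − 4²) × (2² − 1²) = 6 × 9 × 3 = 162.
- Middle pair 4 and 7: 6 × (4² − 3²) × 1 = 6 × 7 = 42.

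The total is 204. By symmetry 204 sets give 2.5. Together 408 / 2,401 = 17.0%, which full enumeration confirms. This shows that the gap is not a rarity of arithmetic. It is not a forecast, because the rating sets will not be equally likely.

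**Step 3: an example that needs no distribution.** Of 25 raters, 15 score 6 or above, 4 score 5.5 and 6 score 3–5.

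| Handling of 5.5 | Core share | Core consensus (≥ 70%) |
|---|---|---|
| Not core, kept in denominator | 15/25 = 60% | no |
| Core | 19/25 = 76% | yes |
| Dropped | 15/21 = 71.4% | yes |

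**Step 4: likely frequency.** Two sets of simulated ratings were used, each rounded to an integer and cut to 1–7.

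- Mean 5.3 to 6.3, SD 1.2, correlation between a panellist's four ratings 0 to 0.9: 5.5 takes about 6% to 26% of votes.
- Mean 5.0 to 7.0, panellist SD 0.8, property noise SD 1.0 or 0.6: about 4% to 18%.

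The share falls as a panellist's four ratings agree more closely and as the mean moves away from the boundary.

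**Step 5: effect on the verdict.** With 25 raters, 70% is 17.5, so core consensus needs 18 votes. For core share p, the chance is P(X ≥ 18) with X binomial (25, p). With panellist SD 0.8 and noise SD 1.0:

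| Mean rating | Share at 5.5 | p, 5.5 not core | p, 5.5 core | Chance, not core | Chance, core | Gap (points) |
|---|---|---|---|---|---|---|
| 5.0 | 16% | 23% | 39% | 0% | 0.1% | 0.1 |
| 5.5 | 18% | 41% | 59% | 0.2% | 13% | 13 |
| 6.0 | 16% | 61% | 77% | 18% | 80% | 62 |
| 6.5 | 11% | 79% | 89% | 85% | 99.7% | 14 |
| 7.0 | 6% | 90% | 96% | 99.8% | 100% | 0.2 |

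At mean 6.0, dropping the 5.5 votes gives about 63%. With noise SD 0.6, the gap is 53 points at mean 6.0 and 5 points at mean 6.5. The gap is large only where the two versions of p lie on either side of 70%.

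**The case against.** Four points can be made for the plan.

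*The literal text already gives an answer for core and excluded.* A 5.5 vote is still a vote but is not in 6–7, so it stays in the denominator and does not count towards core. This is a fair reading, and in the example it gives the same 60% as the fix below. But the article never says that some votes may belong to no category, and its wording has every summary score placed in one of the three. The literal reading also leaves such votes out of the further-discussion count, which can decide whether an item is re-rated or goes straight to the meeting. So the reading narrows the ambiguity without removing it.

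*Items that miss consensus are not lost.* This stands. Under Stopping rules, Round 2 and Step 4, they are re-rated and, if still open, discussed and voted on. A reader might infer that the handling of 5.5 yields a different final framework from the same ratings. The documents do not support that: it changes an item's route, and final inclusion also depends on later rating and voting.

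*The size rests on a near-worst case.* This also stands. A reader might take the contrast of 18% with 80% as typical, or assume that most relevant items will score at the boundary. The article gives no rating distribution, and the contrast shrinks to almost nothing at means of 5.0 and 7.0.

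*A rule may exist in material not shown.* The article cites S3 Appendix for details of the rating properties, and the Fig 2 graphic is missing. A convention could be there, so it cannot be claimed that none exists. Still, the article sets out score, cut-points and threshold itself, and these do not fit together. If a rule exists elsewhere, it should be repeated there.

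**Conclusion.** The gap is certain and follows from the article's own definitions: 2.5 and 5.5 are possible panellist scores without a category. Its frequency is uncertain. Under the assumed distributions, roughly 4% to 26% of votes would be 5.5. With 25 raters, the difference in the chance of core consensus between counting 5.5 as core and not core runs from about 0 to about 60 percentage points, and is large only for items whose core share is near 70%. These sizes rest on assumed, rounded-normal ratings and on half of 50 registered panellists taking part.

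The consequence is limited to whether an item is settled in the survey or continues to Round 2 and the meeting. With those later steps in place, this should be fixed before Round 1, but it does not undermine the design.

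**What to change.** Before Round 1, add one sentence under Defining consensus so that the categories cover every half point: a panellist median of 2 or less is excluded; 6 or more is core; anything strictly between 2 and 6, including 2.5 and 5.5, is further discussion and stays in the denominator. This keeps the Fig 2 caption's floor of moderately relevant for a core item. Give the Fig 2 caption the same cut-points, and report a sensitivity analysis that counts 5.5 as core.

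Any single rule stated in advance would remove the ambiguity. This one is suggested because it agrees with the caption and with the literal reading for core and excluded items. The cost is a sentence and a line of code. The downside is that slightly fewer items reach core consensus than if 5.5 were rounded up.
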